## Abstract

**Background:**

Augmented reality (AR) is a new technology that increases users’ perception of the real world. The purpose of this study is to evaluate the efficacy and safety of augmented reality navigation system in treatment with craniofacial fracture reduction.

**Methods:**

This will be a single-center prospective randomized controlled trial. Twenty-two patients will be assigned to two groups of 11, and those with zygomaticomaxillary complex fractures will undergo preoperative three-dimensional CT modeling and have operational plans designed. The control team will use traditional optical navigation to perform the surgery, and the experimental team will use an AR navigation system. The primary outcome measures will be the accuracy of the key points of surgical area between the preoperational surgical plan and post-operation. The secondary outcome measures will be the blood loss, operation time, bone reduction time, hospital time, and complication rate. The findings obtained through this study are expected to evaluate efficacy and safety of the augmented reality navigation system in the treatment of zygomaticomaxillary complex fractures.

**Discussion:**

This controlled trial of augmented reality navigation system in treatment with zygomaticomaxillary complex fracture reduction will clarify the efficacy and safety of this technology by measuring the accuracy of the key points of surgical area and blood loss, operation and bone reduction times, hospital stay duration, and complication rates. This is a single-center study, and the results are expected to promote the application of augmented reality in craniofacial fracture reduction to improve surgery accuracy and efficacy.

**Trial registration:**

Chinese Clinical Trial Registry ChiCTR1900022626. Registered on April 19, 2019.

## Introduction

### Background and rationale {6a}

The zygomaticomaxillary complex (ZMC) is an integral part of the facial skeleton. There are four articulations in the anatomy of ZMC including the zygomaticosphenoid suture, zygomatic arch with an articulation with the temporal bone, zygomaticomaxillary buttress, and the zygomaticofrontal suture. A bony fracture of the ZMC can damage one or more of the four articulations causing functional and cosmetic problems [1–5].

In traditional ZMC fracture reduction surgery, surgeons usually conduct the preoperative surgical simulation mentally to determine the correct operational procedure and ensure the success of the operation. As a result, the quality of the surgical plan often depends on the surgeon’s own clinical experience and surgical skill, and it is difficult for every member of the surgical group to share that information about the surgical plan [6–10].

Several techniques are used for accurate ZMC fracture reduction, but there are still many problems needed to be solved such as surgical navigation, virtual surgery planning, and a three-dimensional (3D) printing template [11–13]. Augmented reality (AR) is a new technology that increases users' perception of the real world through real and virtual information provided by computer systems. The three characteristics include combining the real and virtual, real time inter-reactivity, and registration in 3D [14].The emergence of AR technology, which uses computers instead of surgeons to carry out the 3D conception of surgical plans, is objective and quantifiable and can be shared by other members of the surgical community.

Recent reviews indicate that AR could provide benefits that address the challenges of conventional navigation systems, such as hand-eye coordination and depth perception [15–19]. The AR study was started in craniofacial surgery. Similar studies have demonstrated the efficacy of the AR system in treating hemifacial microsomia [20], orbital hypertelorism [21], craniosynostosis [22], and craniofacial contouring surgery [23]. While there was a study on the application of AR to the treatment of unilateral orbitozygomatic maxillary complex fracture [24], it was a single-arm study with small sample size. Thus, the purpose of this randomized controlled study is to evaluate the efficacy and safety of AR system in treatment with craniofacial fracture reduction.

### Objectives {7}

The purpose of this study is to (1) achieve real-time tracking and dynamic display using an optical marker plate based on the previous developed augmented reality system [25] and (2) evaluate the application effect of this system in ZMC fracture reduction. Through the elaboration of the research methods and results of this topic, this study may provide surgeons with more intuitive medical information and operable method guidance to help surgeons improve the safety and success rate of ZMC surgery.

### Trial design {8}

This is a single-center prospective randomized controlled trial, performed in an academic hospital. The two parallel groups in this study include the experimental group patients receiving the AR assistant surgery and the control group to be treated with traditional navigation surgery. The allocation ratio of the two parallel groups is 1:1. The trial framework can be seen in Fig. 1.

**Fig. 1 Fig1:**
[figure not shown]
The trial framework. AR, augmented reality

## Methods: participants, interventions, and outcomes

### Study setting {9}

Patients with ZMC fracture reduction included in this study are from Shanghai 9th People’s Hospital, School of Medicine, Shanghai Jiao Tong University, which is an academic hospital. The protocol has been registered in the Chinese Clinical Trial Registry center (ChiCTR) with number of ChiCTR1900022626. (https://www.chictr.org.cn/showproj.aspx?proj=38142)

### Eligibility criteria {10}

The inclusion criteria will include (1) preoperative and postoperative three-dimensional head computerized tomography (CT) scans, (2) unilateral zygomaticomaxillary complex fractures of less than 1 month history with no other surgical treatment, (3) no serious underlying diseases or contraindications, (4) no sex restriction with ages from 15- to 65-years-old, and (5) signed informed consent.

The exclusion criteria include (1) compression fractures, fractures older than one month, (2) complex repair surgery requirement, (3) concurrent disease with contraindications for general anesthesia, and (4) no informed consent.

The withdrawal criteria will include (1) failure to receive treatment as planned, (2) patient request to withdraw from the clinical study, and (3) those lost to follow-up.

### Who will take informed consent? {26a}

The trained investigator in the surgical team will introduce the trial to the patients who meet the inclusion criteria and obtain the written consent from the patients that agree to participate.

### Additional consent provisions for collection and use of participant data and biological specimens {26b}

Not applicable as no biological specimens would be collected.

### Interventions

#### Explanation for the choice of comparators {6b}

The control group is treated without the augmented reality for the surgical navigation during the reduction surgery which means that the surgical plan is decided mentally by the surgeon and only optical tracking is used in the operation procedure. This is the traditional treatment for craniofacial reduction surgery.

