#### Intervention description {11a}

All patients will undergo a 3D CT scan before surgery (LightSpeed 16, GE, Milwaukee), and the data will be stored in DICOM format. All the digital material will be imported into the corresponding processing software (Mimics 21.0, Materialise, Belgium). In the intervention group, two marker plates will be designed based on the coronal incision that can be fixed on the corresponding bone structure with fixation nails to simultaneously track the fracture block and the whole craniofacial bone (Fig. 2). To ensure the real-time tracking of the markers by the camera, the two-sign plate complexes will be positioned in a parallel arrangement two cm away from the bone surface and oriented as parallel as possible to the coronal surface of the skull (Fig. 3). All marker complexes are obtained using 3D printing (ProJet 660 Pro, 3D Systems, South Carolina) and sterilized before surgery. HoloLens was selected as the hardware support (HoloLens, Microsoft, Washington), and the selected development platform was Unity, written in C# language (Unity, Microsoft, Washington). Tracking will be performed through the Vuforia SDK, which stores the feature points of the logo board in the Vuforia engine database in advance. The video camera of HoloLens is used to track the environment, and the system will continually extract original features from the environment and match them with the template in the database. When matching is successful, the system triggers the display of the model in the set position, which is fixed with the position of the marker board, so the tracking frame rate was guaranteed.

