**Fig. 2 Fig2:**
[figure not shown]
Preoperational surgical design (intervention group). **A** Key points for the fracture bone (red point) and the expected reduction location (green point). **B** Tracking plates for the preoperational design (blue and green rectangles)

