**Fig. 3 Fig3:**
[figure not shown]
Preoperational design and the matched augmented reality in surgery by 3D printing plates. **A** Preoperational surgical design. **B** Three-dimensional printing tracking plate in the operation for real-time augmented reality tracking system

The control team will use traditional ZMC fracture reduction surgery.

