### Outcomes {12}

#### Primary outcome measures

The primary outcome measures will be the accuracy of the key points of surgical areas between preoperational surgical plan and post-operation.

All patients will undergo 3D CT examination 1 week after surgery. The preoperative and postoperative image data will be imported into 3D processing software (Geomagic Control X, 3DSystem, South Carolina). The preoperative and postoperative images will be registered, and the accuracy of the selected fracture points will be measured (Fig. 4). To avoid subjective bias error in measurement, the measurement of this part will be made by the trained engineers who do not participate in the operation and are blinded about the allocation. The measurement will be repeated three times and the average value will be taken as the final data.

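### The protocol contradicts itself on the reference for the primary outcome: both arms are scored against a preoperative plan, but the control plan is said to be made mentally

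*Protocol article*

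**What the plan says.** **Outcome.** Outcomes {12} states: "The primary outcome measures will be the accuracy of the key points of surgical areas between preoperational surgical plan and post-operation". The definition carries no restriction by arm. It recurs in the Abstract, in {18a} and in Data management {19}. The Fig. 4 caption also compares the plan with the one-week CT without naming an arm.

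**Evidence that controls have a designed plan.** The Abstract (Methods) says, before it separates the arms, that "those with zygomaticomaxillary complex fractures will undergo preoperative three-dimensional CT modeling and have operational plans designed". It then gives controls optical navigation, as does Trial design {8}. Intervention description {11a} says "All patients will undergo a 3D CT scan before surgery", with the digital data then loaded into the processing software. Sample size {14} assumes 2 ± 0.3 mm in controls.

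**Evidence that they do not.** Section {6b} says of the control arm that "the surgical plan is decided mentally by the surgeon and only optical tracking is used in the operation procedure". The Background {6a} describes traditional surgery as simulated in the surgeon's head. The figure showing key points and target locations is captioned "Preoperational surgical design (intervention group". The only description of the control procedure in {11a} is "The control team will use traditional ZMC fracture reduction surgery".

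The article does not say which stored plan serves as the reference for a control patient.

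**The concern.** A distance from plan to result needs planned coordinates. If a control patient's plan exists only in the surgeon's mind, there are two possibilities. The outcome cannot be scored for that patient, or someone must draw a target by a different process, or at a different time, from the AR target. In the second case the error in the reference differs between the arms and becomes part of the treatment contrast. It would inflate the apparent AR benefit if it moved control targets away from the achieved positions. It would hide a benefit if control targets were drawn with the postoperative result in view. Randomisation does not protect against this, because the error enters through measurement after allocation, and no analysis of the recorded distances can remove it. The planned effect is only 0.4 to 0.5 mm, so a small reference error matters.

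**Working it through.** **1. The sections side by side**

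| Place | Plan in control arm |
|---|---|
| Abstract, Methods | Designed; no limit by arm |
| {6b} | Mental |
| {6a}, on traditional surgery | Mental |
| {11a}, text | Traditional surgery; no digital plan described |
| Fig. 2 caption | Digital targets labelled for the intervention group |
| {12}, {18a}, {19}, Fig. 4 | Needed as the reference; source not stated |
| {14} | 2 ± 0.3 mm, which presupposes a measurable reference |

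The Abstract and {6b} cannot both describe the plan that controls are scored against, unless {6b} means only what guides the surgeon during the operation. The article does not say so.

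**2. The plan's own power figure**

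Inputs from {14}: n = 10 per arm, SD 0.3 mm, two-sided α = 0.05, equal-variance t-test (df = 18).

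- Standard error of the difference = 0.3 × √(2/10) = 0.134 mm.
- Noncentrality at 0.4 mm = 0.4/0.134 = 2.98; power from the noncentral t = 80.491%.
- Noncentrality at 0.5 mm = 0.5/0.134 = 3.73; power = 94.081%.

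Both stated figures reproduce. The sample-size arithmetic is not in question.

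**3. Illustration: systematic offset in the control reference, no true AR effect**

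The offsets are assumptions; the documents give none. The calculation is that of step 2, with the offset b in place of the true difference.

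| Assumed b (mm) | b/0.134 | Chance of p<0.05 |
|---|---|---|
| 0 | 0 | 5% |
| 0.1 | 0.75 | 10.9% |
| 0.2 | 1.49 | 29.2% |
| 0.3 | 2.24 | 56.2% |
| 0.4 | 2.98 | 80.5% |

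The last row equals the planned power by construction: an offset as large as the planned effect is detected as often as the effect would be.

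**4. Illustration: purely random extra error in the control reference**

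Control SD = √(0.3² + e²), with the two variances averaged (approximate), at a true difference of 0.4 mm.

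| Assumed e (mm) | Control SD (mm) | Power |
|---|---|---|
| 0 | 0.300 | 80.5% |
| 0.1 | 0.316 | about 78% |
| 0.2 | 0.361 | about 72% |
| 0.3 | 0.424 | about 63% |
| 0.4 | 0.500 | about 54% |

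This treats the error as adding spread only. In that case the loss is in power, not validity.

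**The case against.** The strongest reply is that a control reference probably exists. The Abstract designs plans before splitting the arms, all patients are scanned, and the sponsor can quote a control value from its own experience. In {11a} the step expressly reserved for the intervention group is the marker plates, and the caption of Fig. 2 may carry its label because of the plates in panel B. Section {6b} may describe what the surgeon works from, not what the measurer scores against. A condensed article may also leave planning logistics to the full protocol.

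Much of this stands. It rules out saying that controls certainly lack a reference. It does not remove the conflict, because {6b} is a positive statement about the control plan and not a missing detail.

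A reader might infer more than the text supports:

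- **That the outcome measures movement achieved, not error against plan.** {12} does say "The preoperative and postoperative images will be registered, and the accuracy of the selected fracture points will be measured", but each of {12}, {18a} and {19} defines the outcome against the plan, and Fig. 4 agrees. The registration wording describes alignment.
- **That the measurer is unblinded by tracking plates in the AR design file.** Nothing says such a file reaches the measurer, and {12}, {16b} and {17a} state that the measurer is blinded. This justifies a precaution, not a finding.
- **That the trial is flawed because it cannot separate AR display from digital planning.** The Objectives {7} aim to evaluate the system in use, and system against usual practice is a legitimate contrast.

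**Conclusion.** The protocol contradicts itself on the reference for its primary outcome, and the consequence is conditional. If {6b} describes practice, the control arm has no fixed reference or one made differently, and the primary comparison is open to an arm-specific bias. If the Abstract describes practice and plans are made identically in both arms, the comparison stands. A reader might conclude that the primary result is not interpretable whatever was done. The documents do not support that, given the Abstract, the common preoperative imaging and the assumed 2 ± 0.3 mm in controls.

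The possible size is known only as an illustration: rejection rates of about 11%, 29%, 56% and 80% for assumed offsets of 0.1 to 0.4 mm with no true effect. These rest on 10 scored patients per arm, SD 0.3 mm in both arms and an offset confined to controls. Neither the presence nor the direction of an offset can be read from the documents. The point still needs settling before analysis, because it concerns what the primary outcome is measured against.

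**What to change.** Reconcile the Abstract, {8}, {6b}, the Fig. 2 caption and the control description in {11a} on whether control patients have a digital plan and what the control surgeons use. Which practice applies is for the sponsor to say. Then state in {6b}, {11a} and {12} that:

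1. each patient's digital reference plan and key-point targets are produced by the same process, in the same software, in both arms;
2. they are fixed before allocation, which Table 1 allows, with screening at day −7 and allocation at day 0;
3. for patients already treated (Trial status gives April 2019 as the start of recruitment), the plan is made from the preoperative CT alone by a planner blind to allocation and to the postoperative CT;
4. both arms are scored as that plan versus the postoperative CT, whether or not the operating surgeon uses the plan.

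As a precaution, give the measurer the plan in one bone-only format for both arms.

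The cost is protocol wording plus digital planning for about 11 control patients, whose preoperative CT data are already to be loaded into the software under {11a}. Plans made afterwards for treated patients are a second best to plans fixed in advance, and the report should say how many were made that way.

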#### Intervention description {11a}

All patients will undergo a 3D CT scan before surgery (LightSpeed 16, GE, Milwaukee), and the data will be stored in DICOM format. All the digital material will be imported into the corresponding processing software (Mimics 21.0, Materialise, Belgium). In the intervention group, two marker plates will be designed based on the coronal incision that can be fixed on the corresponding bone structure with fixation nails to simultaneously track the fracture block and the whole craniofacial bone (Fig. 2). To ensure the real-time tracking of the markers by the camera, the two-sign plate complexes will be positioned in a parallel arrangement two cm away from the bone surface and oriented as parallel as possible to the coronal surface of the skull (Fig. 3). All marker complexes are obtained using 3D printing (ProJet 660 Pro, 3D Systems, South Carolina) and sterilized before surgery. HoloLens was selected as the hardware support (HoloLens, Microsoft, Washington), and the selected development platform was Unity, written in C# language (Unity, Microsoft, Washington). Tracking will be performed through the Vuforia SDK, which stores the feature points of the logo board in the Vuforia engine database in advance. The video camera of HoloLens is used to track the environment, and the system will continually extract original features from the environment and match them with the template in the database. When matching is successful, the system triggers the display of the model in the set position, which is fixed with the position of the marker board, so the tracking frame rate was guaranteed.

**Fig. 2 Fig2:**
[figure not shown]
Preoperational surgical design (intervention group). **A** Key points for the fracture bone (red point) and the expected reduction location (green point). **B** Tracking plates for the preoperational design (blue and green rectangles)

**Fig. 3 Fig3:**
[figure not shown]
Preoperational design and the matched augmented reality in surgery by 3D printing plates. **A** Preoperational surgical design. **B** Three-dimensional printing tracking plate in the operation for real-time augmented reality tracking system

The control team will use traditional ZMC fracture reduction surgery.

#### Criteria for discontinuing or modifying allocated interventions {11b}

The criteria for discontinuing or modifying include the malfunction of AR system, surgical accident, and any situation that make the surgeon need to finish the surgery as soon as possible. The demographic data of the patients who meet those criteria will still be collected.

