### Sample size {14}

This experiment is a single-center prospective randomized controlled trial. Because this kind of experiment has not been carried out previously, the calculated number of samples mainly refers to the previously related published literature [20–24]. With the approval of the ethics committee, the number of patients in each group needs to be 10 for the primary outcome to be statistically significant; meaning a total of 20 patients is needed. The estimated primary outcome of experiment team is 1.5 to 1.6 ± 0.3 mm, while the controlled team value is 2 ± 0.3 mm according to our previous clinical experience. Given the sample size with 10 patients in each group, it achieves 80.491% power to reject the null hypothesis of equal means when the population mean difference is 0.4 with a standard deviation for both groups of 0.3 and with a significance level (α) of 0.050 using a two-sided two-sample equal-variance *t*-test. This sample size achieves 94.081% power to reject the null hypothesis of equal means when the population mean difference is 0.5 with a standard deviation for both groups of 0.3 and with a significance level (α) of 0.050 using a two-sided two-sample equal-variance *t*-test. To allow for a 10% potential dropout rate, the target sample size of this study will be set to 22.

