#### Methods in analysis to handle protocol non-adherence and any statistical methods to handle missing data {20c}

In this trial, the analysis will be performed based on the intention to treat (ITT) principle. The ITT will also be used to deal with those who meet withdrawal criteria, including their demographic data. In case of missing data, the statistician will adopt the last observation carried forward (LOCF) to complete the analysis.

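### The protocol conflicts on whether patients whose allocated procedure is stopped or modified keep their outcome data, so the intention-to-treat comparison of accuracy is not secured

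*Protocol article*

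**What the plan says.** Four places in the protocol article bear on a patient whose allocated procedure could not be completed as intended.

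- **Eligibility criteria {10}:** "The withdrawal criteria will include (1) failure to receive treatment as planned". Patient request and loss to follow-up are the other two criteria.
- **Stopping or changing the procedure {11b}:** the triggers stand in one sentence, shown here up to its closing words on urgent completion: "The criteria for discontinuing or modifying include the malfunction of AR system, surgical accident, and any situation that make the surgeon need to finish". On data from these patients the section says: "The demographic data of the patients who meet those criteria will still be collected".
- **Primary outcome measures (under {12}):** "All patients will undergo 3D CT examination 1 week after surgery". No exception is made for discontinued or modified cases.
- **Handling of non-adherence and missing data {20c}:** "the analysis will be performed based on the intention to treat (ITT) principle". It continues: "The ITT will also be used to deal with those who meet withdrawal criteria, including their demographic data". For missing data, "the statistician will adopt the last observation carried forward (LOCF) to complete the analysis".

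**The concern.** Intention to treat needs the outcome of every randomised patient, whatever happened in theatre. Demographic data cannot support a comparison of accuracy, blood loss, operation time or complications. Section {11b} is the one place that deals directly with data from failed procedures, and it names demographics and stops there. Section {10} adds a withdrawal rule that an AR case finished without AR would fit. Site staff following those two sections could reasonably stop collecting outcomes. Staff following the outcome section and {20c} would carry on.

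One of the three triggers, AR malfunction, is a failure of the technology under test and cannot occur in the control arm. If such cases leave the analysis, the comparison becomes AR when it worked against all controls, and it no longer rests on the randomisation. With 11 patients per arm, one or two cases matter.

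**Working it through.** **1. The sections side by side, for a patient whose allocated procedure was stopped or changed**

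| Section | What it implies |
|---|---|
| {10} | Fits a withdrawal criterion on plain reading |
| {11b} | Demographics collected; outcomes not mentioned; not called withdrawn |
| Primary outcome, {12} | Has the 1-week CT like everyone else |
| {11c}, {18b} | 6 months of follow-up for each patient |
| {20c} | Analysed by intention to treat, demographics included; gaps filled by LOCF |

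No section says that outcomes of these patients are discarded. None says outright that they are kept and analysed in the allocated arm.

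**2. Can LOCF close the gap?** Accuracy is the deviation of the post-operative result from the plan. Table 1 schedules it once, after surgery, so there is no earlier value to carry forward. A missing CT stays missing.

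**3. The plan's own figures.** Section {14} gives: "The estimated primary outcome of experiment team is 1.5 to 1.6 ± 0.3 mm, while the controlled team value is 2 ± 0.3 mm". For the two-sided equal-variance t-test with 10 per group (18 df), the noncentrality is difference / (SD × √(1/10 + 1/10)):

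- 0.4 / (0.3 × √0.2) = 2.981, power 80.491%
- 0.5 / (0.3 × √0.2) = 3.727, power 94.081%

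Both match the protocol, and 20 × 1.1 = 22 gives the stated total. The planning values are therefore a fair base for an illustration.

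**4. Loss of power is minor.** At a difference of 0.4 mm with 11 controls, power is 84.5%, 82.5%, 80.1% and 77.2% with 11, 10, 9 and 8 AR patients. The risk is bias.

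**5. Possible shift in the estimate.** The documents give no failure rate and no accuracy for failed cases, so both are assumptions here. Let k of 11 AR cases fail and end at a mean of m mm, with the other AR cases at 1.6 mm and controls at 2.0 mm. The as-randomised AR mean is ((11 − k) × 1.6 + k × m) / 11. For k = 2 and m = 2.5 this is (14.4 + 5.0) / 11 = 1.764, a difference of 0.236 mm. If the failed cases are left out, the difference is 2.0 − 1.6 = 0.40 mm in every row.

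| Failed AR cases | m = 2.0 | m = 2.5 | m = 3.0 |
|---|---|---|---|
| 1 | 0.364 | 0.318 | 0.273 |
| 2 | 0.327 | 0.236 | 0.145 |
| 3 | 0.291 | 0.155 | 0.018 |

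**6. Possible false findings.** Suppose AR has no benefit over all its patients (overall mean 2.0 mm). The retained AR cases then average (22 − k × m) / (11 − k); for k = 2, m = 3.0 this is 16 / 9 = 1.778 mm. With SD 0.3 mm and 100,000 simulated trials per setting, dropping the failures gives a significant result in AR's favour (nominal 2.5%) in:

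| Dropped | m = 2.0 | m = 2.5 | m = 3.0 |
|---|---|---|---|
| 1 | 2.5% | 5.5% | 10.8% |
| 2 | 2.5% | 12.1% | 34.2% |
| 3 | 2.5% | 24.4% | 71.7% |

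**The case against.** The strongest reply is that the protocol never says outcomes are dropped. A reader might infer from {11b} that demographics are all that is kept, but the word *only* is not there. Section {20c} speaks of demographics as included in what is analysed, which suggests more than demographics. The CT and the 6-month follow-up are ordered for all patients, and {22} has complications in either group recorded and reported. If those sections prevail, intention to treat is feasible, so it cannot be said that the stated analysis is impossible or that complications after conversion are hidden. Nor does {11b} itself call these patients withdrawn. All of this stands.

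The direction of bias is also not established. Surgical accident and hurried completion can occur in either arm, and nothing shows that AR malfunction is the most frequent trigger. The illustration rests on assumed inputs. A failed case at 3.0 mm lies (3.0 − 2.0) / 0.3 = 3.3 SD above the control mean. If failed cases do no worse than controls, two of them move the difference only from 0.40 to 0.33 mm and the false-positive rate is not raised.

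Finally, this is a condensed article, and details of analysis sets may stand in a document not shown. That would answer a complaint about missing detail. It does not answer this one, which is that rules printed in the article point in different directions. A listed withdrawal criterion is a rule someone may apply.

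**Conclusion.** The point holds as a conflict between {10} and {11b} on one side and {12} and {20c} on the other. If the first pair is followed, intention to treat for accuracy is not secured and LOCF cannot rescue it. Exclusion for AR malfunction would then fall on one arm only, and it would favour AR if failed cases are less accurate.

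The size cannot be read from the documents. On the assumed inputs, two failed AR cases ending at 2.0 to 3.0 mm correspond to an as-randomised difference of 0.33 to 0.15 mm, against 0.40 mm without them. A reader might go further and conclude that the plan as written would report 0.40 mm. The documents do not support that: the stated principle is intention to treat, and no section prescribes an analysis restricted to completed procedures.

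**What to change.** Reconcile the four sections. None of this touches when or how a surgeon stops or changes a procedure; it concerns data collection and analysis.

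- **{10}:** remove non-receipt of the planned treatment as a reason for withdrawal from the study and its analysis.
- **{11b}:** replace the sentence on demographics with a statement that the 7-day CT and all perioperative and 6-month outcomes are collected for every randomised patient, including discontinued or modified cases, and analysed in the allocated arm.
- **{20c}:** drop LOCF for accuracy. For any CT that is truly missing, add a sensitivity analysis over a range of plausible values.
- **Reporting:** give the number of AR malfunctions and conversions by arm, so that the reader can see how often the allocated procedure failed.

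The cost is small. The CT and follow-up are already scheduled for all patients, so the change is wording, submitted to the ethics committee as {25} requires. Recruitment is already under way, so the team should also check that outcomes were kept for any procedure already stopped or modified. The estimate may turn out slightly less favourable to AR.
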